When planning infection control measures, it has to be taken into consideration that patients move freely between acute care and rehabilitation facilities, as well as within the ambulant sector [15]. Therefore, hospitals should not be viewed as isolated units, but rather as connected elements of a larger modular network, requiring a regional approach [16]. In the Baltic Sea Coast region, the joint research project HICARE (Health, Innovative Care And Regional Economy) was initiated in 2011 to improve control of MDROs in north-east Germany. HICARE is supported by public funds and supplemented by industrial contributions. A basic element of the HICARE project is the implementation of a multimodal hygiene program in the acute care hospitals of the region, which was developed within the framework of the HICARE project and included all German statutory specifications for infection protection. The governmental recommendations for the prevention and control of multiresistant organisms are mandatory for medical facilities, as specified by the July 2011 revision of the German *Infection Protection Act* (Infektionsschutzgesetz) [17]. To date, nationwide mandatory recommendations have been issued for MRSA [18–20] and, more recently, for MRGN [9, 21]. In addition to these two groups of causative organisms, the HICARE program includes recommendations for dealing with VRE.

To include the patient’s point of view and experience, the current study contains a patient evaluation sheet on hospital hygiene practice, and examines as well the health-related quality of life of patients with MDROs. Only few studies have been published on these aspects. Analyses of the costs and benefits of measures to reduce multidrug-resistant organisms are also scarce in Germany [22, 23].

One problem that arises with pre- and post-studies to determine the effects of intervention measures is the fact that changes in statutory requirements over time often affect the results. Therefore, the present study is designed as a prospective, controlled intervention study. Since the goal is to implement the HICARE hygiene program in all participating hospitals, those in the control group will obtain the intervention measures immediately after completion of the study phase I (delayed-intervention group; see also Fig. 2).

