### Methods of data collection and variables

Baseline data collection conducted with participating hospitals included a questionnaire to assess structural parameters (e.g. number of beds/cases/single rooms, staffing ratio, staff level of qualification, prevalence of advanced training in hygiene), and process parameters (procedures of registering, documentation and reporting of MDROs). At the end of each study phase (Fig. 2), potential changes in structural or process parameters were documented, together with use of antibiotics and disinfectants for the given period.Data on the use of antibiotics and disinfectants over the three years prior to this study, as well as test utilization and resulting positive MDRO rates, were documented by the study team.The level of knowledge of the nursing staff and physicians on MDROs was assessed by a multiple choice test at the beginning of the instructional courses.Structured questionnaires and documentation forms were used during the intervention period, and, for the delayed-intervention group only, during the observation period, identical for all hospitals (Table 3).

**Table 3 Tab3:** Documents used for data acquisition during the intervention and observation phase

Documents used in the intervention and observation phase	Description of data collected	Document to be filled out by
Patient admission sheet	Risk factors for MDRO colonization or infection	Health care workers during anamnesis, or, alternatively, by the patient (with help of staff)
Documentation sheet on the progression of MDRO status including transition section^**a**^ for the physician responsible for subsequent treatment	Admission and discharge data, sample taking and diagnosis, where applicable isolation measures, control swab test, time of infection, information for physician responsible for subsequent treatment	Health care workers
Documentation sheet for nursing efforts for MDRO^b^ infections/colonizations	Nursing workload in minutes	Nursing staff
Patient evaluation sheet	Subjective evaluation of hygiene measures in the hospital	Patient
Quality of life questionnaire (modified version of the SF-36)	Health-related quality of life in the last seven days	Patient

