### Data analysis

#### Sample size

According to German screening recommendations on MRSA, about 40 % of patients admitted in acute hospitals in Germany have risk factors for MRSA [32]. It has been shown that screening recommendations are not followed completely, despite their obligatory character [33]. Based on information solicited with our institutional questionnaire, not all of the participating hospitals had fully adapted to the recommendations at baseline. Thus, as basis for sample size calculations, our intervention was assumed to improve the screening rate in MRSA risk patients from 60 % (control group) to 90 % (intervention group). The expected sample of > 1000 patients in each group results in a very high statistical power (approaching 1.0) for this study (type-I risk: 0.05).

With an observation period of six months for each of the 24 participating wards, at least 5,000 patient admissions with an anticipated stay over 48 hours are expected. Based on previous examinations [7, 8, 34, 35], an MRSA prevalence at admission of approximately 1 to 3 % is anticipated. Accordingly, 50 to 150 MRSA positive patients would be eligible for follow-up examinations.

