#### Data analysis

To evaluate the effect of the outcome measures, a hierarchical logistic regression model for the log-odds of a patient’s chance to be screened for either MRSA, VRE, or MRGN was formulated as follows:

(level 1):$$ \mathrm{logit}{\left( antibiogram=1\right)}_{ij}={a}_j+{\beta}_1{X}_{1ij}+{\beta}_2{X}_{2ij}+\cdots +{\varepsilon}_{ij} $$

with$$ \begin{array}{l}\mathrm{i}:=1\kern0.28em \mathrm{t}\mathrm{o}\kern0.28em \mathrm{k}\kern4.5em \mathrm{patient}\kern.3em \mathrm{i}\mathrm{ndex}\kern1em \\ {}\mathrm{j}:=1\kern0.28em \mathrm{t}\mathrm{o}\kern0.24em 8\kern4.5em \mathrm{ID}\kern.3em \mathrm{number}\kern0.28em \mathrm{o}\mathrm{f}\kern0.28em \mathrm{hospital}\kern1em \\ {}{\mathrm{X}}_1\kern0.28em \mathrm{t}\mathrm{o}\kern0.28em {\mathrm{X}}_{\mathrm{m}}\kern4.8em \mathrm{i}\mathrm{ndividual}\kern.3em \mathrm{patient}\kern0.28em \mathrm{c}\mathrm{hartacteristics},\mathrm{such}\kern.2em \mathrm{a}\mathrm{s}\kern.2em \mathrm{a}\mathrm{ge},\mathrm{sex},\kern.2em \mathrm{s}\mathrm{urgical}\kern0.28em \mathrm{t}\mathrm{reatment}\kern.2em \mathrm{e}\mathrm{t}\mathrm{c}.\kern1em \end{array} $$

As the intervention program was implemented on the level of participating hospitals, the following level-2 equation (random intercept model) was a priori specified for statistical analysis:$$ {a}_j={\gamma}_{00}+{\gamma}_{01}{\zeta}_{1j}+{\gamma}_{02}{\zeta}_{2j}+\cdots +{\omega}_j $$

with γ_00_ representing the global base rate parameter for screening tests, and γ_0j_ hospital-specific additions depending on the intervention group (ζ_1_ = 1 for intervention period, 0 otherwise), hospital capacity (ζ_2j_ measured on metric scale level) or similar. To test the main hypothesis, the significance of parameter γ_01_ (deviation from zero) will be tested. Control for potential center effects is exerted by introduction of the ω_j_ center-specific error terms of the intercept parameter.

It will be decided during the model selection process whether or not other variables on the hospital level are to be introduced in separate level-2 equations as so-called random slope-effects (e.g. hospital-specific tendencies towards testing older patients more frequently).

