### Strengths and limitations

An intervention with such a wide approach has strengths, but it also has limitations. One strength of this project is that by contributing to the regional management of MDROs, other regions can profit from the findings on the implementation of the structure and processes. On the other hand, possible effects of the study cannot be ascribed to individual interventions, but rather are the result of the total intervention program combined with changes motivated by external factors, including campaigns initiated by the local government, or regional public health offices. The nested studies are designed to provide insight into the cost-benefit aspects, the health-related quality of life, as well as the risk profiles of the various MDROs. The HARMONIC study has a highly interdisciplinary basis, providing insight into medical and nursing care, epidemiology and health economics. These may provide a basis for decisions in health care policies.

A limitation of our study is that it was not possible to provide direct financial support to the hospitals for the additional cost incurred by the implementation of the program. It was therefore necessary to find a workable model that could be implemented within the framework of daily hospital routine. Consequently, it was necessary for certain aspects to fall back on the current documentation of the hospital; e.g. for microbiologic results, it was necessary to rely on the hospital laboratory rather than on the installation of a central diagnostics. This could, however, prove to be a strength in the long run, as we had to find solutions that are likely to be sustainable under routine conditions.

The following factors were taken into consideration in the conception of the HARMONIC study:Limitations of staffing resources (e.g. for documentation of hygiene measures)Limitations of financial resources (e.g. for additional screening examinations)Structural factors of the hospitals (e.g. number of single rooms, staff / patient ratio)

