The HICARE hygiene management system was tailored to the possibilities and requirements of the individual hospitals by a mutual coordination process. The results of this coordination are documented in detail and will be taken into consideration in the evaluation of the project. This approach was designed to achieve a regional standard for hygiene recommendations based on scientific evidence that is affordable for the hospitals. Close collaboration with the staff responsible for hygiene and with the policy makers of the hospitals should ensure that these hygiene measures will be sustainably implemented after the end of the study. Despite the limitations, we believe that with the design of this study and the chosen parameters, the groups will be comparable.

An important topic would be the incidence of MDROs before and after the intervention. Unfortunately, our investigation does not collect sufficient data to analyze questions referring to MDRO incidence. Due to limited financial resources, as mentioned above, we were not able to conduct additional diagnostics to analyze this outcome.

In 2011, parts of the German infection protection act were changed and further complemented in 2013. The law says that the heads of defined medical institutions have to ensure that measures according to the current standard of medical science have to be applied to prevent the spread of nosocomial infections, especially those with multidrug resistance. It is assumed that this standard is applied when the recommendations of the “commission for hospital hygiene and infection protection” are considered. In the HARMONIC study, we support regional acute hospitals to implement those recommendations timely and effectively, implementing consistent processes that can be adapted to local challenges, and managed and monitored. Nevertheless, at least some of the control hospitals are assumed to have already implemented the national recommendations. However, the extent may differ due to limited strategic resources, so an improvement as a result of our intervention is expected.

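### The primary model names no phase term: if the delayed hospitals' second phase enters coded as intervention, the test of γ₀₁ becomes mainly a before-after comparison

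*Protocol article*

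**What the plan says.** The protocol article, Background, explains the controlled design: in pre-post studies "changes in statutory requirements over time often affect the results". Hospitals are therefore randomised within four matched pairs to start at once or six months later (Design overview and setting), and the delayed group receives the programme after the first phase.

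Patients on the selected wards are monitored for six months in each phase (same section). Under Methods of data collection and variables, the patient forms are used in the intervention period and, "for the delayed-intervention group only, during the observation period".

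The Data analysis section gives a random-intercept logistic model whose level-2 equation is declared a priori. It holds an intercept, ζ₁, hospital capacity or a similar covariate, and a hospital error term. The coding is "ζ_1_ = 1 for intervention period, 0 otherwise". The test is stated as: "To test the main hypothesis, the significance of parameter γ_01_ (deviation from zero) will be tested". Neither level names a phase or calendar term. The only model-selection step described concerns random slopes.

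The Sample size section counts "With an observation period of six months for each of the 24 participating wards".

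**The concern.** The coding is by period, and the delayed hospitals pass through both kinds of period. Read literally with two-phase data, they have ζ₁ = 0 in phase I and ζ₁ = 1 in phase II. In those hospitals ζ₁ then coincides exactly with calendar phase. A random intercept per hospital makes the within-hospital contrast far more precise than the randomised 4-versus-4 contrast, so the within-hospital contrast receives nearly all the weight.

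Without a phase term, a rise in screening that occurred everywhere would be credited to the programme, and the randomised concurrent comparison would hardly contribute to the main test. The article itself regards external change as possible. It says "In 2011, parts of the German infection protection act were changed and further complemented in 2013", and it attributes any effect to the programme "combined with changes motivated by external factors".

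**Working it through.** **The plan's own figure.** Eight hospitals with three wards each give the 24 wards. At least 5,000 admissions × 40% at risk = 2,000, or 1,000 per group. For 60% against 90%, SE = √(0.6·0.4/1000 + 0.9·0.1/1000) = 0.0182, and 0.30/0.0182 = 16.5, so power is effectively 1, as stated. This count uses one six-month period per ward, which is the phase I parallel comparison.

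**Layouts if both phases enter.**
- A: immediate hospitals in phase I only (ζ₁ = 1); delayed hospitals in phase I (0) and phase II (1).
- B: as A, with immediate hospitals also in phase II (1).

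**Inputs.** From the article: 4 + 4 hospitals, 60% screened under control. Assumed: n = 250 risk patients per hospital and phase (1,000/4), or 100; between-hospital SD τ on the logit scale; a common shift δ from phase I to phase II; no programme effect. The sampling variance of one hospital-phase logit is s² = [1/(0.65·0.35)]/n = 4.396/n, which is 0.01758 at n = 250.

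**Two contrasts feed γ₀₁ when there is no phase term.**
- Within delayed hospitals: variance W = s²/2; it picks up +δ.
- Between groups, scaled to estimate γ₀₁: in A, variance B = 2τ² + 1.5s², picking up −δ; in B, variance B = 2τ² + s², picking up 0.

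The weight on the within contrast is w = B/(B + W). The share of δ read as programme effect is 2w − 1 in A and w in B.

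Example (A, n = 250, τ = 0.5): W = 0.00879; B = 0.5 + 0.02637 = 0.52637; w = 0.9836; share = 0.967. SE = √(WB/(W + B)) = 0.093.

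| τ | A, n=250 | B, n=250 | A, n=100 | B, n=100 |
|---|---|---|---|---|
| 0 | 0.50 | 0.67 | 0.50 | 0.67 |
| 0.2 | 0.85 | 0.92 | 0.74 | 0.85 |
| 0.3 | 0.92 | 0.96 | 0.84 | 0.91 |
| 0.5 | 0.97 | 0.98 | 0.93 | 0.96 |
| 0.8 | 0.99 | 0.99 | 0.97 | 0.98 |

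**Effect on the test** (A, n = 250, τ = 0.5, two-sided 5%). Common rises from 60% to 63%, 65% and 70% are δ = 0.127, 0.214 and 0.442. Then z = 0.967·δ/0.093 = 1.32, 2.22 and 4.60, so an ineffective programme is declared effective in about 26%, 60% and over 99% of trials. Simulated maximum-likelihood fits of the logistic model gave 27%, 58–67% and 96% or more.

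**With a phase term, or phase I only.** Both groups are compared in the same phase, so the share of δ is 0. At n = 250 and τ = 0.5:
- Phase I only, or A with a phase term: SE = √((τ² + s²)/2) = √(0.26758/2) = 0.37.
- B with a phase term: variances s² = 0.01758 and 2τ² + s² = 0.51758 combine to SE = 0.13.

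**The case against.** The strongest reply is that the article never says phase II records enter the primary model. Three features favour a parallel reading. ζ₁ⱼ carries only a hospital subscript, so a hospital cannot formally take both values. The hospital-level additions are introduced as depending on intervention group. The Sample size section contrasts a control group with an intervention group over a single six-month period. On that reading a common trend does no harm. The figure showing the phases is not available, and the covariate lists are left open-ended. All of this stands, and it makes the bias conditional.

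It does not remove the point. The coding names a period, the delayed hospitals supply data in both periods, and no sentence limits the test to phase I.

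A reader might also infer that external change is documented between the phases. It is not. The statutory change is dated only to 2013, while collection began in February 2013, and the campaigns are undated. Nor is near-complete absorption general: it needs a between-hospital SD of about 0.3 or more at 250 patients per hospital and phase.

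**Conclusion.** The point holds in conditional form. As printed, the specification permits an analysis in which γ₀₁ is mainly a before-after contrast in four hospitals, contrary to the article's own reason for having controls. In that analysis γ₀₁ absorbs roughly 92–99% of a common trend under the central assumptions and at least half under every setting in the table. The hospital SD, patients per hospital and phase, and trend size are assumptions, since the article gives none of them. Marked differences between hospitals in size and in baseline adoption of the recommendations make zero between-hospital variance implausible.

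The stronger conclusions, that the primary analysis is a pre-post comparison or that a positive result would be spurious, are not supported. The parallel reading remains open, and no trend of known size is shown.

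**What to change.** State in the Data analysis section that γ₀₁ is tested on the phase I parallel comparison, which is the one the Sample size section sizes. Alternatively, if both phases enter, index ζ₁ by hospital and phase and add a fixed phase or calendar-time effect. Under either choice, report the delayed hospitals' before-after change separately as an uncontrolled secondary result.

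A mean-zero hospital-by-phase random effect is not a substitute. Adding a variance of 0.2² to 0.3² to s² in the formula for layout A, with τ of 0.3 to 0.8, still leaves 73–96% of a common trend in γ₀₁.

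The change is about one sentence and needs no new data. The price is precision: at τ = 0.5 the standard error rises from about 0.09 to about 0.37 logits if only phase I is used or immediate hospitals have no phase II data, or to about 0.13 with a phase term if they do. The precision given up came from the contrast that is confounded with time.

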## Methods and design

### Design overview and setting

A total of 12 hospitals providing acute care participate in the HICARE project. Due to lack of personnel and time resources, four of these hospitals could not participate in the HARMONIC study. Therefore, the study was conducted in eight hospitals in the Health Region Baltic Sea Coast in Germany (Fig. 1). The study was designed as an 18-month prospective intervention study, which aims at implementing a multimodal hygiene management program. The recruitment of study hospitals started right after ethics approval (29th of May 2012). Hospitals were randomized concerning the immediate implementation of the intervention program *versus* the campaign starting with a six-month delay, in four strata of two hospitals each. The strata were defined by level of care (maximum care *versus* standard care) and hospital size (>25,000; 10,000 to 25,000; 5,000 to 10,000; and < 5,000 annual discharges). Table 1 shows the characteristics used to match the participating hospitals in according pairs. The hospitals in the delayed-intervention group received the intervention measures after completion of the first phase of the study (Fig. 2). Data collection started in February 2013 and was finished for the main study in November 2014. Analysis will be finished in June 2015 and December 2015 for two of the nested studies.

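### The tested intervention covariate is defined both as a group and as a period, with no phase term; if the delayed hospitals' phase II patients enter the model, most of any time trend passes into the effect estimate

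*Protocol article*

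**What the plan says.** The Data analysis section gives a hierarchical logistic model for the chance of being screened, with a random intercept per hospital, and presents the hospital-level equation as fixed in advance.

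- **Covariate in words:** "hospital-specific additions depending on the intervention group".
- **Covariate in the parenthesis that follows:** 1 "for intervention period, 0 otherwise".
- **Covariate in the equation:** ζ₁ⱼ, with j running over the 8 hospitals and no time index.
- **Other hospital-level terms:** capacity, "measured on metric scale level) or similar". Phase and calendar time are not mentioned.
- **Left to model selection:** "whether or not other variables on the hospital level are to be introduced in separate level-2 equations", that is, random slopes.
- **Test:** "To test the main hypothesis, the significance of parameter" γ₀₁.

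On the design, Design overview and setting states: "The hospitals in the delayed-intervention group received the intervention measures after completion of the first phase of the study". It adds that wards were monitored for six months in each phase. Methods of data collection and variables says the patient forms were used in the intervention period and, "for the delayed-intervention group only, during the observation period". The Background justifies a controlled design by noting that, in pre-post studies, "changes in statutory requirements over time often affect the results".

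**The concern.** Every hospital has an intervention period, and a delayed hospital also has an observation period. Under the parenthesis, a delayed hospital is therefore 0 in phase I and 1 afterwards. The equation cannot express this, because each hospital has a single value of ζ₁ⱼ. No sentence says which phases enter the primary test.

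The choice matters because the model has a hospital intercept and no time term. A change within a hospital is free of between-hospital variance, so it is far more precise than the comparison of 4 with 4 hospitals. Once both phases of the delayed hospitals are in the data, the fit relies mainly on their before-after change. Any general rise in screening between the phases would then be counted as an effect of the programme. That is the weakness the Background says the controlled design was chosen to avoid.

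**Working it through.** **1. The plan's own figure.** The Sample size section gives 60% versus 90%, more than 1,000 patients per group and type-I risk 0.05 (taken as two-sided), with power approaching 1.0. Treating patients as independent:

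- SE under the null: √(2 × 0.75 × 0.25 / 1000) = 0.0194
- SE under the alternative: √[(0.60 × 0.40 + 0.90 × 0.10) / 1000] = 0.0182
- (0.30 − 1.96 × 0.0194) / 0.0182 = 14.4, so power is 1.000

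The figure reproduces. It says nothing about time trends, but it does indicate a layout: 0.40 × 5,000 admissions = 2,000 risk patients, which is 1,000 per group or 250 per hospital for one six-month period.

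**2. Assumptions.** The article gives no ICC, so 0.01 to 0.20 is used, with τ² = ICC/(1 − ICC) × π²/3. Hospitals are taken as equal in size. The sampling variance of one hospital-phase log-odds is s² = 1/(250 × 0.60 × 0.40) = 0.0167. The figure showing the study phases is not available, so the phase II role of the immediate hospitals was varied.

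**3. Share of a phase II shift that reaches γ₀₁, with period coding and no phase term.**

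Suppose first that the immediate hospitals supply phase I only. Two independent estimates of the effect are available:

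- The delayed hospitals' before-after difference has variance s²/2 and absorbs +1 times the shift.
- Twice the difference between the immediate mean and the delayed two-phase mean has variance 2τ² + 1.5s² and absorbs −1 times the shift.

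Inverse-variance weighting gives a net share W = (τ² + s²/2)/(τ² + s²).

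If the immediate hospitals are observed in both phases and coded 1 throughout, the second estimate has variance 2τ² + s² and absorbs none of the shift. Then W = (τ² + s²/2)/(τ² + 0.75s²).

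| ICC | τ² | W, immediate in phase I only | W, immediate in both phases |
|---|---|---|---|
| 0.01 | 0.0332 | 0.0415/0.0499 = 0.83 | 0.91 |
| 0.05 | 0.1732 | 0.1815/0.1898 = 0.96 | 0.98 |
| 0.10 | 0.3655 | 0.3739/0.3822 = 0.98 | 0.99 |
| 0.20 | 0.8225 | 0.8308/0.8391 = 0.99 | 0.995 |

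The share is 0 if only phase I is analysed. It is also 0 if the immediate hospitals' phase II patients are coded 0, because the shift then cancels, but that coding labels hospitals already given the programme as unexposed.

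**4. Effect on the test.** The random-intercept logistic model was simulated with a true effect of zero, immediate hospitals in phase I only, ICC 0.01 to 0.10, 300 runs per setting and a Wald test.

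| Assumed background change | Log odds ratio of the trend | Mean estimate | Declared significant |
|---|---|---|---|
| none | 0 | 0.00–0.01 | 4–6% |
| 60% to 65% | 0.214 | 0.19–0.20 | 54–58% |
| 60% to 70% | 0.442 | 0.40–0.43 | 98–99.7% |

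With phase I only (ICC 0.05, 200 runs), the mean estimate stays at about 0 despite the trend.

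**5. Price of removing the bias.** A fixed phase effect brings W to 0. The SE of the log odds ratio changes as follows:

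| ICC | Pooled, no phase term | Phase term, immediate in phase I only | Phase term, immediate in both phases |
|---|---|---|---|
| 0.01 | 0.087 | 0.158 | 0.118 |
| 0.05 | 0.090 | 0.308 | 0.126 |
| 0.10 | 0.091 | 0.437 | 0.128 |

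The third column equals the phase-I-only comparison, √[(τ² + s²)/2]; at ICC 0.05 this is √(0.1898/2) = 0.308.

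**The case against.** The strongest reply is that the article intends a concurrent comparison. The sentence says group before it says period, ζ₁ⱼ carries only a hospital index, and within phase I the two descriptions coincide. The sample size contrasts a control group with an intervention group and fits one six-month period. On that reading a common trend does not bias the test. All of this stands. A reader might infer that the plan has settled on a pooled analysis and given up the randomised comparison, but the documents do not support that.

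A second reply is that an article may leave the choice of phases to an analysis plan. That would excuse silence. Here the article states a coding rule, presents the model as fixed in advance, and gives a rule that conflicts with its own equation and misleads if applied literally to all monitored patients. The open-ended hospital-level terms do not settle it either, since those named are hospital characteristics.

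A reader might also infer that the 2013 addition to the infection protection act fell between the phases. The Discussion gives only the year, and data collection began in February 2013, so the timing is unknown. The trend sizes used here are illustrations, not forecasts.

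**Conclusion.** The point holds in conditional form. The Data analysis section does not fix whether ζ₁ is a group or a period indicator, nor which phases enter the primary test, and it names no time term. If the delayed hospitals' phase II patients are included, as the period definition implies, 83–99% of a background shift is reported as intervention effect, and a rise of 5 percentage points gives false-positive rates of about 54–58%. If only phase I is used, this bias is zero.

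These sizes rest on the assumed ICC, equal hospital sizes, 250 risk patients per hospital and phase, and the assumed trend. The conflict between definition and equation rests on the text alone. It needs correcting because one reading gives a randomised contrast and the other mostly an uncontrolled before-after change, and the two can lead to opposite conclusions.

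**What to change.** State that the primary test of γ₀₁ is the concurrent phase I comparison of immediate with delayed hospitals, with ζ₁ⱼ as group indicator, and delete the period wording.

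If both phases are to be used, index ζ₁ by hospital and phase, add a fixed phase effect and a hospital-by-phase random term, and code immediate hospitals as exposed in any later phase.

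The change is one of wording; no new data are needed. The cost is precision: at ICC 0.05 the SE rises from 0.090 to 0.308 with phase I only, or to 0.126 if immediate hospitals are observed in both phases. These SEs include no hospital-by-phase variance, which would widen the interval further and would be hard to estimate from eight hospitals.

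The correction does not solve a separate problem. With only eight hospitals, the Wald test rejected in 17–22% of null runs for phase I alone (ICC 0.05), and in 7–24% with a phase term and immediate hospitals in phase I only. The reference distribution should allow for the small number of hospitals.

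### The primary effect is a hospital-level coefficient tested on eight hospitals with no small-sample reference stated; an uncorrected z test in a parallel, unpaired comparison would have a true size of about 10-18% instead of 5%

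*Protocol article*

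**What the plan says.** **Design.** Under Design overview and setting, "the study was conducted in eight hospitals in the Health Region Baltic Sea Coast in Germany". They were randomised to an immediate or a six-month delayed start "in four strata of two hospitals each", so four hospitals against four.

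**Planned error and power.** Under Sample size, screening of MRSA risk patients is assumed to improve "from 60 % (control group) to 90 % (intervention group", with "type-I risk: 0.05". The power statement is: "The expected sample of > 1000 patients in each group results in a very high statistical power (approaching 1.0) for this study". Neither the number of hospitals nor any between-hospital variance enters it.

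**Model.** The Data analysis section gives a patient-level logistic equation and a hospital-level equation for the intercept. The second contains the intervention indicator ζ1, hospital capacity on a metric scale, an open-ended allowance for comparable terms, and a hospital error term. It is described as follows: "random intercept model) was a priori specified for statistical analysis". No pair or stratum term is named.

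**Test.** "To test the main hypothesis, the significance of parameter" γ01 (its deviation from zero) is what will be examined. The type of test and its reference distribution are not given.

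**What stays open.** "It will be decided during the model selection process whether or not other variables on the hospital level are to be introduced" as random slopes. In addition, ζ1 is described as reflecting the intervention group but is coded by intervention period, and the design section says wards were followed for six months in each phase.

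**The concern.** γ01 compares hospitals, so its precision depends on how much eight hospitals differ, however many patients each supplies. With intervention alone in the hospital equation, 6 between-hospital degrees of freedom remain; with capacity, 5. The usual large-sample test of a mixed-model coefficient treats the between-hospital variance as known and, under maximum likelihood, also underestimates it. Both faults make a nominal 5% test reject too often.

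This is the only primary hypothesis. Pair randomisation allows 2^4 = 16 allocations, so the smallest two-sided randomisation p-value is 2/16 = 0.125. Significance at 5% therefore depends entirely on the parametric reference distribution. Extra hospital terms or random slopes chosen after seeing the data would draw on the same few degrees of freedom.

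**Working it through.** **Inputs from the article:** 8 hospitals, 4 pairs, 60% versus 90%, more than 1000 patients per group, α = 0.05. **Assumptions:** two-sided test (sidedness is not stated); for simulation, about 250 risk patients per hospital and a between-hospital SD of 0.2 to 1.0 on the logit scale.

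**1. The article's power figure.** Treating patients as independent, z = 0.30 / √[(0.6×0.4 + 0.9×0.1)/1000] = 0.30/0.0182 ≈ 16.5, so power is 1.000. The figure reproduces, but only for independent patients. It says nothing about the error rate of a hospital-level test.

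**2. True size of an uncorrected z test, large hospitals.** Each hospital contributes one log-odds. With an unbiased residual variance (residual sum of squares/df) the statistic follows t on df degrees of freedom, so size = P(|t_df| > 1.96). Maximum likelihood divides by 8 instead of df, so size = P(|t_df| > 1.96·√(df/8)).

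| Hospital-level terms | df | Unbiased variance | ML cut-off on t scale | ML variance |
|---|---|---|---|---|
| Intervention | 6 | 9.8% | 1.96·√(6/8) = 1.70 | 14.1% |
| Intervention + capacity | 5 | 10.7% | 1.96·√(5/8) = 1.55 | 18.2% |
| Intervention + one further covariate beyond capacity | 4 | 12.2% | 1.96·√(4/8) = 1.39 | 23.8% |
| Intervention + fixed pair terms | 3 | 14.5% | 1.96·√(3/8) = 1.20 | 31.6% |

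**3. Simulation of the parallel comparison** (random-intercept logistic model, maximum likelihood, 1000 runs per scenario, control rate 60%, no true effect):

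- No pair similarity, intervention only: Wald z 13-15%.
- No pair similarity, with capacity: Wald z 17-20%. The top value arises when hospital sample sizes follow the discharges in Table 1.
- The likelihood ratio test in these scenarios ran at about 10-15%, so the problem is not peculiar to the Wald test.
- Using t critical values but keeping the ML standard error still gave 7-12%, so the variance needs correcting as well as the reference distribution.

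**4. Effect of leaving out the pairs.** With half the hospital variance lying between pairs and no pair term, Wald z size was 6% (intervention only) or 11% (with capacity). With most of the variance between pairs it was about 4% (with capacity). Ignoring effective pairing lowers the size. Adding fixed pair terms under a plain z raises it, as the last table row shows.

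**5. Effect of the period coding.** If delayed hospitals enter in both phases with capacity in the model and no period term, Wald z size was 5% with no trend and no hospital-by-period variation, 27% with a hospital-by-period SD of 0.2 logit, and 53% with a secular trend of 0.2 logit. The trend and SD values are assumptions.

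**6. Critical values.** t at 0.975 is 2.447 (6 df), 2.571 (5 df) and 3.182 (3 df). Divided by 1.96 these give 1.25, 1.31 and 1.62.

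**The case against.** The strongest objection is that the article never says a z test will be used. A reader might infer that the trial's 5% test really runs at 10-18%. The text does not support that: it names no Wald statistic, no variance estimator and no reference distribution, and a condensed article may leave these to a full plan that is not shown. The figure is conditional on an uncorrected test.

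Three other inferences also go too far:

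- **That omitting the pairs inflates the error.** Step 4 shows the opposite. Capacity also partly adjusts for size, one of the two stratification factors.
- **That the hospital-level model as a whole is chosen from the data.** The random-intercept equation is declared in advance. Only its open-ended covariate list and the random slopes are undecided, and none of the 10-18% comes from model selection.
- **That 10-18% describes whatever is analysed.** It assumes each hospital sits in one arm. If delayed hospitals contribute both periods, step 5 applies, and the size could be near 5% or far above 18%.

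The between-hospital SD and the equal 250 patients per hospital are also not in the article; they are assumptions. The analytic figures in step 2 need neither, only hospitals large enough for sampling error within them to be small.

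What stands is that the article does not simply defer the primary analysis. It writes out the equations, names the parameter and states the error rate. The usual large-sample test of that parameter does not hold that rate with eight hospitals.

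**Conclusion.** The concern holds in conditional form. The primary hypothesis rests on a hospital-level coefficient informed by eight hospitals in four pairs, and no small-sample reference is stated. With an uncorrected z test, a parallel four-versus-four comparison and paired hospitals no more alike than others, the nominal 5% test has a true size of about 10-11% (unbiased variance) to 14-18% (ML variance), and the interval is too narrow. With effective pairing and no pair term the size was about 4-11%, so the error rate depends on an unknown pair similarity unless the handling of pairs is stated. The open covariate list and the data-driven random slopes ask more of eight hospitals than they can give; their effect on the error rate was not quantified. Whether the model covers phase I alone or both phases must be settled before any single size can be attached to the test.

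**What to change.** Before analysis, state the following in the Data analysis section:

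1. **Comparison.** The primary analysis is the parallel phase-I comparison. If delayed hospitals are to enter in both periods, add a period term and allow for hospital-by-period variation.
2. **Level-2 terms.** Intervention plus at most one named covariate, with the open-ended wording removed and random slopes reported as sensitivity analyses only.
3. **Test.** Refer γ01 to a t distribution with between-hospital degrees of freedom, using a restricted-likelihood-type variance, or use a t-test on hospital-level adjusted log-odds.
4. **Pairs.** Choose one handling in advance and show the other as a sensitivity analysis:
   - unpaired: 6 df, or 5 with capacity; critical value 2.45-2.57;
   - paired: 3 df, fewer if capacity is kept; critical value 3.18.

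   These are different analyses and should not be presented as equivalent.

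The cost is wording and precision; no new data are needed. Compared with a 1.96 interval on the same standard error, the interval is about 25-31% wider unpaired or about 62% wider paired. The paired choice recovers some of this only to the extent that paired hospitals are truly alike.
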